### 2.3 Sample size

According to G*Power software, we need 21 participants per group to obtain a power of .95 to detect a mean effect size of .37 (based on well-being outcomes in mindfulness retreats, [11]), using order of intervention as a between-subject factor (MBSR first vs CCT first) and time as a within-subjects factor (5 times of assessment), with an alpha of .05, a power 95%, and a 2-tailed test. In anticipation that there may be last-minute dropouts in pre-registrants or incomplete data in the sample collection or the analysis of the planned psychological or biological data, we have increased the sample by an additional 20% to 26 participants for each condition (52 in total). This sample size further corresponds to the average size of standard meditation retreats [11, 41] and in studies of brain activity in meditators [29, 30].

### 2.4 Components and structure of the programs

Each program will comprise standard MBSR and CCT protocols in an intensive format to fit a retreat mode. Throughout the retreat, participants will be in silence, not talking to each other or using electronic devices. Each program will last 3 days in total, and all participants will go through both programs. On each retreat day, participants will spend a total of 4.25 hours of sitting meditation, 2 hours of walking meditation, 2 hours of explanations and discussing with the instructors, doubts or problems related to the practices, and 1 hour of mindful body movements (yoga/qigong). In total, participants will have 9 hours of practice each day. (A description of the contents of the programs is shown in Table 1).

**Table 1 pone.0283169.t001:** Description of the main practices of the retreat.

Practice	Description	Protocol	Day
**Basics of Mindfulness**	Practices and insights into mindfulness and acceptance. In this part, explanations are given on how to approach practices during the retreat, and how to deal with distractions, unpleasant bodily experiences, or difficult emotional states.	MBSR / CCT	1
**Yoga-Qigong**	Simple body exercises to relax tensions, unblock joint patterns, and develop mindfulness in movement. In the case of CTT, references are also made to self-care and self-compassion in movement.	MBSR / CCT	1
**Walking meditation**	The participant is trained in the ability to be aware while walking. The movement is slower than usual. Breathing and walking movements are integrated. In the MBSR protocol, awareness of the breath and the body is encouraged. In CCT, loving-kindness or compassion is developed while walking.	MBSR / CCT	2
**Body Scan**	Attention is brought to the various parts of the body. From the soles of the feet to the top of the head. The aim is to develop mindfulness. Every time there is a distraction, the attention is gently taken up again on the sensations of the body.	MBSR	1
**Awareness of Breathing**	Attention is focused on breathing. Two options are given, depending on the preference of the participants (i.e., focusing attention on the tactile sensations of air in the nostrils or on the sensation of the movement of the abdomen).	MBSR	2
**Awareness of Thoughts**	It aims to focus attention on the activity of the mind (i.e., on the spontaneous generation of thoughts and emotions).	MBSR	3
**Open Monitoring**	It is about accounting for the constant flow of subjective phenomena: cognition, perception, and emotion. Rather than choosing an object to focus attention, participants are encouraged to engage in a choiceless awareness in which subjective experience is continuously monitored.	MBSR	3
**Loving-kindness and compassion for a loved one**	Through visualization exercises of loved ones, practitioners are helped to recognize feelings of love whenever they arise.	CCT	1
**Self-Compassion**	Practising through assertions generates a feeling of self-acceptance and a desire to overcome suffering.	CCT	2
**Loving-kindness for one-self**	Meditation practices are aimed at teaching appreciation and gratitude for oneself through visualization and verbalization.	CCT	2
**Common humanity**	Through visualization practices, a sense of interconnectedness is developed (i.e., the knowledge that experiences of suffering are inherent to all human beings, as well as the pursuit of happiness).	CCT	2
**Compassion for others**	Through visualizations and verbalizations, it aims to develop compassion for others. Starting with a loved one, continuing with neutral people, and culminating with people with whom one has difficult relationships.	CCT	3
**Active compassion practice**	A practice known as *tonglen* in Tibetan Buddhism, it aims to develop a sense of compassion towards others. The participant visualizes how he or she can reduce suffering in other people by doing something beneficial for them.	CCT	3

#### 2.4.1 Mindfulness-Based Stress Reduction (MBSR)

The MBSR is an 8-week standardized program [42] that aims to cultivate awareness by paying attention to the present moment with acceptance and a non-judgmental disposition. Training is delivered by two certified instructors at the University of Massachusetts Centre for Mindfulness (**Error! Hyperlink reference not valid.**
www.umassmed.edu/cfm/) and Mindfulness Center at Brown University (https://www.brown.edu/public-health/mindfulness/home).

#### 2.4.2 Compassion Cultivation Training (CCT)

The CCT is an 8-week standardized program [3, 43] aimed at cultivating compassion and empathy toward oneself and others, consisting of daily formal and informal practices. Training is delivered by two certified instructors at the Compassion Institute and Nirakara-Lab.

### 2.5 Study outcomes

#### 2.5.1 Epigenetic changes

Samples of peripheral blood will be obtained and processed in situ, during the retreat. Participants’ blood samples will be collected in two standard tubes (10ml each) that contain EDTA as an anticoagulant. Blood samples will be processed immediately using the standardized Ficoll gradient centrifugation protocol to isolate mononuclear cells. These cells are cryopreserved directly (with 10% DMSO culture medium) and stored appropriately (in a -80 C freezer for short periods and liquid nitrogen for longer storage). Nucleic acids will be extracted in the laboratory of the Biomedical Epigenetics group, IDIBAPS (Barcelona), using DNA and RNA extraction kits. Once the nucleic acids are obtained, they will be stored in suitable freezers (-20 or -80°C) until their use for molecular profiling techniques, such as DNA methylation arrays (Infinium Methylation EPIC Bead Chip from Illumina, herein called “EPIC methylation arrays”), and gene expression by massive RNA sequencing (RNA-seq). (See Table 2).

**Table 2 pone.0283169.t002:** Study procedures at specific time points.

		7-day retreat			
	Home baseline screening	Day 1^st^ (BL)	Day 4th	Day 7th	3- and 12-month follow-up
** *Epigenetic measures* **					
• DNA methylation levels		x	x	x	
• Proportion of main blood cell types		x	x	x	
• Epigenetic clocks		x	x	x	
** *Psychological measures (outcomes of programs)* **					
• Perceived Stress Scale	x				
• Depression Anxiety Stress Scales (DASS-21)		x	x	x	x
• Patient Health Questionnaire (PHQ-15)	x			x	x
• Patient Health Questionnaire (PHQ-9)	x			x	x
• Satisfaction with Life Scale (SWLS)	x			x	x
• State Difficulties in Emotion Regulation (S-DERS-21)		x	x	x	x
• State Mindfulness Scale (SMS)		x	x	x	x
• State Self-Compassion Scale (SSCS)		x	x	x	x
• Fear of Compassion (FOC)		x	x	x	x
• Hedonic and Arousal Affect Scale (HAAS)		x	x	x	x
• Meditation-Related Adverse Effects Scale			x	x	x
** *Psychological tasks* **					
• Arithmetic Stress Test		x	x	x	
• Autobiographical memory retrieval		x	x	x	
• Positive and Negative Affect Schedules (PANAS—state)		x	x	x	
• State-Trait Anxiety Inventory (STAI-20)		x	x	x	
** *Psychophysiological laboratory* **					
• EEG recording (open- and closed-eyes)		x	x	x	
• EKG recording		x	x	x	
• Respiratory rate		x	x	x	
** *Cortisol activity* **					
• Saliva samples (bedtime and awakening)		x	x	x	

Note: BL = Baseline

#### 2.5.2 Psychological measures

*a) Self-report measures*. Most of these measures were developed in studies with the general population and have been also used in previous MBI studies in healthy individuals [22]. They have shown good or excellent psychometric properties and cover selected psychological distress and functioning constructs (i.e., stress, anxiety, depression, mindfulness, compassion, well-being, and emotion regulation) and all will be administered online via Qualtrics with individualized links (Table 2):

*Psychological distress*. Depression Anxiety Stress Scales (DASS-21) [44, 45].*Psychological well-being*. Satisfaction with Life Scale (SWLS) [46, 47].*Mindfulness*. State Mindfulness Scale (SMS) [48].*Anxiety*. State-Trait Anxiety Inventory (STAI-20) [49, 50].*Somatic Symptoms*. Patient Health Questionnaire (PHQ-15) [51, 52].*Sleep difficulties*. DSM-5 sleep difficulties [53].*Compassion*. State self-compassion State Self-compassion Scale (SSCS) [54, 55].*Fear of Compassion*. The Yourself subscale from the Fear of Compassion Scale [56].*Emotion Regulation*. State Difficulties in Emotion Regulation (S-DERS-21) [57, 58].*Current mood*. Positive and Negative Affect Schedules (PANAS) [59, 60].*Daily assessments of psychological functioning*. A 7-item scale to assess participants’ average state of mindfulness, mind wandering, compassion to others, self-compassion, well-being, the richness of life, and utility of the contents of the program every day.*Affect in the last 3 days*. Hedonic and Arousal Affect Scale (HAAS) [61].*Meditation Adverse Effects*. Meditation-Related Adverse Effects Scale–Mindfulness-Based Program (MRAESMBP) [62].*Program satisfaction*. Client Satisfaction Questionnaire (CSQ-8) [63, 64].

*b) Psychological stress tasks*. ***b*.*1) Stress Reactivity*.** Arithmetic Stress Test: a standardized laboratory stress induction procedure, that is part of the Trier Social Stress Test [65, 66], will be used to assess participants’ stress reactivity. Individuals are asked to repeatedly subtract a given 2-digit number (i.e., 13) from a 4-digit number (e.g., 1022). These numbers were changed for each of the three assessment days. Participants are asked to write their responses on a personal computer as quickly as possible. Time is limited to 3 minutes to increase the stressful nature of the task. Pre-post stress level changes in mood will be assessed with the PANAS and STAI.

***b*.*2) Emotion regulation*.** A 10-min retrieval of autobiographical negative memories. Participants will receive a link through Qualtrics for a baseline assessment (three days before the retreat) where they are asked to think about three negative autobiographical memories of events for which they felt responsible and made them feel negative emotions such as shame, guilt, and sadness. Participants will be asked to assign personal keywords (e.g., ‘traffic accident’), for each of the three memories, synthesizing the event. Each of the three negative events will be randomly assigned to the three respective assessment days so that participants were given the corresponding “keywords” when they begin the retrieval task. Participants are given 10 minutes to write down the memory as specifically as possible. Pre-post changes in their sadness, happiness, anxiety, serenity, shame, and guilt affect states will be assessed using a 0 (nothing) to 100 (very much) visual analog scale. These two laboratory psychological tasks will be completed by each individual while alone in a quiet room, using a portable computer.

#### 2.5.3 Neurobiological laboratory measures

*a) Brain electrical activity*. Recording of EEG activity in resting state (alternating open and closed eyes, 6 min each condition) with four EE-225 64chEEG+24chBIP 16kHz devices with a laptop and eego EEG recording software. The sampling rate will be set at 1000 Hz and the reference is 7Z of the equidistant layout.

*b) Respiratory activity*. Respiration rate, which is related to attention training and psychological well-being [67], will be monitored by a respiration chest-band, during the EEG assessment session and will be registered using a piezoelectric sensor.

*c) Cardiac activity*. EKG activity will be monitored with dedicated electrodes during the EEG assessment session. Based on these recordings, we will analyze changes in EKG, heart rate, and heart rate variability (HRV) patterns

These recordings will be completed by everyone in laboratory spaces dedicated to the EEG assessments.

#### 2.5.4 Salivary sampling and cortisol measurement

Participants will be given Salivette® cortisol saliva sample collection tubes (Sarstedt, Germany) that contain a sterile cotton swab for sample absorption along with detailed verbal and written instructions concerning sample collection. Diurnal Cortisol Slope and cortisol levels at bedtime and awakening will be measured at three different time points of the retreat (see Fig 1). Then, the saliva samples will be stored in the refrigerator until they are delivered to the laboratory after a few hours. Once in the laboratory, the samples will be centrifuged at 3000 rpm for 5 min, resulting in around 1.5–2.0 ml clear supernatant of low viscosity that will be stored at −80°C until the analyses of the salivary cortisol levels. Cortisol, the principal stress glucocorticoid produced by the hypothalamic-pituitary-adrenal axis (HPA) [68], will be assessed using a commercially available enzyme-linked immunosorbent assay (Salimetrics®) having an approximate sensitivity of <0.007 μg/dL.

Table 2 shows a description of all measures and time points.

### 2.6 Procedure

In arriving at the retreat centre, everyone will be informed about the retreatment rules (e.g., accommodation, silence rules, use of electronic devices, etc.) as well as his/her specific time schedules for each of the laboratory sessions. All laboratory sessions will be done on the morning of each assessment day. We will set up different laboratories for the tasks (one for blood extractions, one with nine computers to complete the self-report questionnaires, four EEG separate labs with portable equipment, and another four separate labs for the psychological tasks with one computer per room). The schedule of the assessments will be kept the same for each participant on the three assessment days. The order of the tasks will be the same for all participants (i.e., blood extraction, self-report questionnaires, EEG recording, autobiographical memory task, and arithmetic stress task). The expected total duration of each assessment session is approximately 90 minutes.

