As, to the best of our knowledge, this is the first study using a sequential design with two intensive meditation modalities, it is difficult to formulate specific hypotheses regarding the separate and combined effects of the MBSR and CCT programs on the selected outcomes. Thus, considering the two MBIs jointly, we expect that both programs will significantly: a) modify the DNA methylation and expression levels of specific genes and a reduction of the DNA methylation-based biological clock; b) reduce participants’ levels of psychological distress while increasing their levels of psychological functioning (i.e., mindfulness, compassion, emotion regulation, and well-being); c) change the EEG spectral profile of the resting state brain activity (i.e., changes in the balance between Alpha (8–14 Hz) and Theta (4–8 Hz) frequency bands and, regarding the organization of the brain functional networks, a modulation of the difference between the activation of the default mode network and the one corresponding to the salience network); d) alter awakening and bedtime cortisol levels leading to a steeper Diurnal Cortisol Slope (DCS); e) improve the efficacy of mood regulation following a negative mood induction (using an autobiographical memory task); f) reduce participants’ reactivity in an objective experimental stress test (i.e., Arithmetic Stress Test). In addition, given the multidisciplinary nature of the present project, we intend to provide a comprehensive view of potential changes in various areas of biological and psychological functioning and their interrelationships.

In general, we expect an overall pattern of results in which changes will be significantly higher for the combined effects of both MBIs than for each program separately. Moreover, based on previous literature comparing standard MBSR and CCT programs [24], we expect no major differences in primary outcomes between both programs, although the mechanisms of change may be different; in general, changes in MBSR will be mediated by cognitive variables (e.g., mindfulness) whereas changes in CCT will be mediated by socio-emotional variables (e.g., compassion). We also expect that the self-reported psychological changes associated with the MBIs will remain 3 months after the programs.

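### The memory task has no rating after the post-retrieval one, so hypothesis e cannot separate mood regulation from initial reaction, and the fixed task order leaves hypothesis f open to carry-over that changes over days

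*Protocol article*

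**What the plan says.** Among the expected effects listed in the Introduction, hypothesis e is that the programs will "improve the efficacy of mood regulation following a negative mood induction", with the autobiographical memory task as the induction. Hypothesis f is that they will lower reactivity in the Arithmetic Stress Test.

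Section 2.5.2 b.2 describes the memory task: ten minutes of writing about a personal event chosen for emotions such as shame, guilt and sadness. For its outcome, "Pre-post changes in their sadness, happiness, anxiety, serenity, shame, and guilt affect states will be assessed" on 0 to 100 visual analog scales. No later rating is described. Section 2.5.2 b.1 describes the arithmetic test, which lasts three minutes and has ratings of its own: "Pre-post stress level changes in mood will be assessed with the PANAS and STAI".

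Section 2.6 states that "The order of the tasks will be the same for all participants", and the sequence ends with "EEG recording, autobiographical memory task, and arithmetic stress task". Each participant's schedule is the same on Days 1, 4 and 7. A session takes about 90 minutes, not itemised by task. Both tasks use "another four separate labs for the psychological tasks with one computer per room".

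**The concern.** There are two linked difficulties.

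**Hypothesis e.** The hypothesis is about what happens to mood after it has been lowered. The measurement ends with the rating that closes the induction. A pre-post difference shows how far mood moved by the end of retrieval. It does not show whether the participant regulated the reaction, reacted less in the first place, or engaged less with the memory. If the change shrinks from Day 1 to Day 7, the trial could not say which of these occurred, yet the hypothesis would invite the first reading.

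**Hypothesis f.** The arithmetic pre-rating is taken in people who have just done a task designed to worsen mood. If the programs speed recovery from that task, as hypothesis e implies, the starting point of the arithmetic test shifts over the retreat. The reactivity score could then change without any change in stress reactivity, or a real change could be partly masked.

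**Working it through.** The plan gives no figure to reproduce here. The check compares what each hypothesis needs with what is rated, and then uses two small illustrations. All numerical inputs to the illustrations are assumed, in arbitrary points; none is an estimate for this trial.

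**Step 1: hypothesis e against its ratings.** Let P be the peak mood shift that retrieval would cause if unregulated, and g the share removed by regulation before the post rating. Then

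pre-post change = P × (1 − g).

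| Assumed P | Assumed g | Change |
|---|---|---|
| 20 | 0 | 20 × 1 = 20 |
| 30 | 1/3 | 30 × 2/3 = 20 |
| 40 | 1/2 | 40 × 1/2 = 20 |

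Three different combinations of reaction and regulation give the same outcome. One difference cannot identify two quantities.

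**Step 2: hypothesis f and carry-over.** I read the PANAS/STAI pre-rating as taken just before the arithmetic test, hence after the memory task. Let S be the true stress effect (assumed 15, the same on all days), I the mood shift from the memory task (assumed 20), r the share of I still present at the pre-rating, and q the share of that residue that fades during the test. Then

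observed reactivity = S − q × r × I,

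shift from Day 1 to Day 7 = q × I × (r1 − r7).

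| r1 → r7 | q | Day 1 | Day 7 | Shift |
|---|---|---|---|---|
| 1.0 → 1.0 | 0.50 | 15 − 10 = 5.0 | 5.0 | 0 |
| 1.0 → 0.5 | 0 | 15.0 | 15.0 | 0 |
| 1.0 → 0.5 | 0.25 | 15 − 5 = 10.0 | 15 − 2.5 = 12.5 | +2.5 |
| 1.0 → 0.5 | 0.50 | 15 − 10 = 5.0 | 15 − 5 = 10.0 | +5.0 |
| 0.5 → 0.25 | 0.25 | 15 − 2.5 = 12.5 | 15 − 1.25 = 13.75 | +1.25 |
| 0.5 → 0.25 | 0.50 | 15 − 5 = 10.0 | 15 − 2.5 = 12.5 | +2.5 |

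The shift is zero if nothing is left over, if the same share is left on both days, or if nothing fades during the test. The sign is not fixed either. If leftover negative mood amplifies the response to the next stressor, the term becomes + q × r × I, and the third and fourth rows give −2.5 and −5.0.

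**Step 3: does the plan contain another check?** EKG and respiration are recorded during the EEG session (section 2.5.3), which precedes both tasks (section 2.6), so the arithmetic test has no physiological measure alongside it. The covariates in section 2.7 are age, sex and previous meditation experience, not mood before the test. The PANAS/STAI pre-rating could serve as a delayed mood rating after retrieval, but it uses different instruments, has no stated timing and is not planned for that purpose.

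**The case against.** Much can be said for the plan, and most of it stands.

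- **Timing.** A reader might infer that the arithmetic test starts straight after retrieval with no recovery time. Section 2.6 gives an order, not a timetable. The stated times for EEG, memory and arithmetic add to 6 + 6 + 10 + 3 = 25 of about 90 minutes, and the rest is not broken down. A gap is neither shown nor excluded, and an article may leave it to the full protocol.
- **Reactivity is measured.** A reader might infer that hypothesis f has no valid outcome. The arithmetic test has its own pre and post ratings, so a reactivity score exists. It is exposed to carry-over, not absent.
- **The fixed order protects some contrasts.** Order and schedule are the same on all days and in both groups, so a constant carry-over cancels in the change over time and in the group-by-time comparison. Bias needs a residue that changes over days; bias between the groups needs it to change differently by program sequence.
- **Random allocation of memories.** The three memories are assigned at random to the three days, so their content is balanced over days on average. That does not balance how fully participants engage with the task as it is repeated.
- **Meaning of efficacy.** The Introduction does not define it as recovery after the task, and regulation during retrieval does affect the post rating. True, but Step 1 shows that the post rating cannot isolate it.

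Counterbalancing the two tasks may look like the natural remedy. It would put the memory task after a stressor for half the sample, moving carry-over into hypothesis e, and would leave about 26 / 2 = 13 participants per group and task order.

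**Conclusion.** The point holds in a limited form. For hypothesis e there is a mismatch between hypothesis and measurement that does not depend on any gap between tasks: the two ratings described do not separate regulation from the size of the reaction or from avoidance. For hypothesis f the fixed order means that the pre-rating is not a neutral baseline, and the score is open to carry-over if residual mood changes from Day 1 to Day 7. That condition is what success on e would imply, but nothing in the article shows that it will occur.

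The size and sign of any effect on f cannot be derived from the article. The points in the working rest entirely on assumed values and include zero. A reader might conclude that success on e must hide a benefit on f; the article does not support that, because the direction depends on whether leftover mood fades during the test or amplifies the response. Two of the six listed expectations are touched. This is a worthwhile, low-cost improvement and not a defect that invalidates either task.

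**What to change.** In sections 2.5.2 b.2 and 2.6:

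1. Repeat the six visual analog scales at a fixed, stated time after the post-retrieval rating and before the arithmetic test, for example together with the PANAS/STAI pre-rating. Add a brief neutral interval if room time allows.
2. Define regulation for hypothesis e as the change from the post-retrieval rating to this third rating. Keep the pre-post change and label it mood reactivity. Read the two together, since a small initial shift leaves little to recover.
3. Report hypothesis f by day together with, or adjusted for, mood before the arithmetic test. That mood may itself be changed by the programs, so show the unadjusted result as well.

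The cost is about one minute per session, with no new staff or equipment. Four task rooms for 52 participants means 52 / 4 = 13 sessions per room each morning, so one minute adds about 13 minutes of room time. An assumed five minutes for rest plus rating would add 13 × 5 = 65 minutes, which is why the rest is optional and the rating is not.

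If sessions have already been run, the memory outcome can still be described as mood reactivity, the pre-arithmetic PANAS/STAI ratings reported by day, and the carry-over stated as a limitation, which the Discussion does not now do.
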